**Toxicity Dose Adjustments and Delays of Abemaciclib**

| Toxicity Type                                                                                                | Toxicity Profile and Severity                                  | Dose Suspension                                                                                                                                                                      | Dose Reduction                                                                                                 |
|---------------------------------------------------------------------------------------------------------------------|-----------------------------------------------------------------------|---------------------------------------------------------------------------------------------------------------------------------------------------------------------------------------------|-----------------------------------------------------------------------------------------------------------------------|
| ALT/AST Increased with increased total bilirubin, in the absence of cholestasis
Sections 7.4.1.1.1.4 and 9.4.2.1 | ≥Grade 2 increased ALT/AST (>3.0 x ULN) with total bilirubin >2 x ULN | Abemaciclib therapy MUST be discontinued.                                                                                                                                            | Abemaciclib therapy MUST be discontinued.                                                                      |
| ILD/Pneumonitis
Sections 7.4.1.1.1.5 and 9.4.2.4                                                                 | Grade 2                                                               | Dose MUST be suspended until toxicity resolves to baseline or Grade ≤1. If persisting despite maximal supportive measures for more than 7 days, permanently discontinue abemaciclib. | Dose MUST be reduced by 1 dose level.                                                                          |
|                                                                                                                     | Recurrent Grade 2 or Grade 3-4                                        | Abemaciclib therapy MUST be discontinued.                                                                                                                                            | Abemaciclib therapy MUST be discontinued.                                                                      |
| VTE c
Sections 7.4.1.1.1.6 and 9.4.2.3                                                                | Grade 3 or 4                                                          | Suspend dose and treat as clinically indicated. May resume abemaciclib therapy when participant is clinically stable.                                                                       | Suspend dose and treat as clinically indicated. May resume abemaciclib therapy when participant is clinically stable. |

Abbreviations: ALT = alanine aminotransferase; ASCO = American Society of Clinical Oncology; AST = aspartate aminotransferase; ILD = interstitial lung disease; ULN = upper limit of normal; VTE = venous thromboembolic events.

Note: MAY = per the investigator's clinical judgment; MUST = mandatory.

a Additional guidance for renal and hepatic monitoring is in Sections 9.4.2.1 and 9.4.2.2.

b Determination of persistent events will be at the discretion of the investigator. Recurrent toxicity refers to the same event occurring within the next 8 weeks (as measured from the stop date of the preceding event). As a general guidance, based on the risk/benefit balance assessment per the investigator, for a patient who experiences a new episode of Grade 3 hematological toxicity after more than 8 weeks following the last episode of same Grade 3 hematological toxicity, the investigator may consider resuming the patient on the same drug dose should the patient satisfy the following conditions:

- shows stable hematological counts (Grade ≤2) during that timeframe
- has absence of any signs or risk of infection
- is benefiting from study treatment

c Note: the patient who presents with no liver metastases at baseline.

d Grade 3 ALT/AST increased is a trigger for additional assessments and possibly hepatic monitoring. See Section 9.4.2.1 for additional guidance for hepatic monitoring.

e VTE dose modifications are specifically for patients with breast cancer. Dose modifications for patients with lung cancer who experience VTEs should be managed using the nonhematologic toxicity guidance.

**7.4.1.1.1. Dose Adjustments****7.4.1.1.1.1. Abemaciclib**

Dose adjustments as outlined in Table JPCE.7.3 are allowed both within a cycle and between cycles. Abemaciclib must be reduced sequentially by one dose level.

Abemaciclib dose alterations (omission, reduction, discontinuation) should not be based solely on the presentation of serum creatine values, because these may not reflect actual renal function. Further information can be found in the abemaciclib IB Section 3.2.4.

For patients requiring dose reduction(s), any re-escalation to a prior dose level is permitted only after consultation with the Lilly CRP. After re-escalation, subsequent dose adjustments should be based on the dose of abemaciclib that the patient is currently receiving.

**Table JPCE.7.3. Dose Adjustments of Abemaciclib**

| Dose Adjustment | Oral Dose | Frequency |
|-----------------|-----------|-----------|
| 0               | 150 mg    | Q12H      |
| 1               | 100 mg    | Q12H      |

Abbreviation: Q12H = every 12 hours.

If a patient receiving the 100 mg Q12H dose of abemaciclib requires a further dose reduction, the patient should be discontinued from study treatment. If a patient is, in the judgment of the investigator, receiving clinical benefit from study therapy and requires further dose reduction than what is outlined in [Table JPCE.7.3](#), the investigator must discuss with the Lilly CRP prior to any further dose reduction.

#### **7.4.1.1.1.1. Hematologic Toxicity**

Before the start of each cycle, hematologic toxicity possibly related to abemaciclib must resolve to at least Grade 2. If a patient experiences Grade 4 hematologic toxicity possibly related to abemaciclib, then dosing must be suspended (until the toxicity resolves to at least Grade 2) and the dose of abemaciclib must be reduced by 1 dose level as outlined in [Table JPCE.7.2](#). If a patient experiences Grade 3 hematologic toxicity, then dosing must be suspended (until the toxicity resolves to at least Grade 2) and the dose of abemaciclib may be reduced by 1 dose level as outlined in [Table JPCE.7.2](#) at the discretion of the investigator. If the patient experiences a recurrent episode of Grade 3 hematologic toxicity, then dosing must be suspended (until the toxicity resolves to at least Grade 2) and the dose of abemaciclib must be reduced by 1 dose level as outlined in [Table JPCE.7.2](#).

Recurrent toxicity refers to the same event occurring within the next 8 weeks (as measured from the stop date of the preceding event). As a general guidance, based on the risk/benefit balance assessment per the investigator, for a patient who experiences a new episode of Grade 3 hematological toxicity after more than 8 weeks following the last episode of same Grade 3 hematological toxicity, the investigator may consider resuming the patient on the same drug dose should the patient satisfy the following conditions:

- The patient showed stable hematological counts (Grade  $\leq 2$ ) during that timeframe
- In the absence of any signs or risk of infection
- The patient is benefiting from study treatment

If a patient requires administration of blood cell growth factors, the dose of abemaciclib must be suspended for at least 48 hours after the last dose of blood cell growth factors was administered and until toxicity resolves to at least Grade 2, then must be reduced by 1 dose level, if a dose

reduction for the specific event necessitating the use of the growth factors has not already occurred.

#### **7.4.1.1.1.2. Nonhematological Toxicity**

Before the start of each cycle, nonhematologic toxicity (except alopecia and fatigue) possibly related to abemaciclib must resolve to either baseline or at least Grade 1. If a patient experiences  $\geq$ Grade 3 nonhematologic toxicity (except diarrhea, refer to Section 7.4.1.1.1.3; or ALT/AST increased, refer to Section 7.4.1.1.1.4; or ILD/pneumonitis, refer to Section 7.4.1.1.1.5; or VTE, refer to Section 7.4.1.1.1.6) possibly related to abemaciclib, then dosing must be suspended (until the toxicity resolves to either baseline or Grade 1) and the dose of abemaciclib must be reduced by 1 dose level as outlined in Table JPCE.7.2.

If a patient experiences persistent or recurrent Grade 2 nonhematologic toxicity (except diarrhea, refer to Section 7.4.1.1.1.3; or ALT/AST increased, refer to Section 7.4.1.1.1.4; or ILD/pneumonitis, refer to Section 7.4.1.1.1.5; or VTE, refer to Section 7.4.1.1.1.6) possibly related to abemaciclib that does not resolve with maximal supportive measures within 7 days to either baseline or Grade 1, then dosing must be suspended (until the toxicity resolves to either baseline or Grade 1) and the dose of abemaciclib must be reduced by 1 dose level as outlined in Table JPCE.7.2.

#### **7.4.1.1.1.3. Diarrhea**

A patient experiencing diarrhea requiring hospitalization (irrespective of grade that is, requiring intravenous rehydration) or severe diarrhea (Grade 3 or 4; see Appendix 9) must have study treatment suspended (until the toxicity resolves to either baseline or at least Grade 1) and the dose of abemaciclib must be reduced by 1 dose level as outlined in Table JPCE.7.2. If a patient experiences Grade 2 diarrhea that does not resolve with maximal supportive measures (refer to Section 7.7.1.1.1) within 24 hours to at least Grade 1, the study drug must be suspended (until the toxicity resolves to at least Grade 1) but abemaciclib dose reduction is not required. However, if a patient experiences persistent or recurrent Grade 2 diarrhea that does not resolve with maximal supportive measures (refer to Section 7.7.1.1.1) within 24 hours to at least Grade 1, then study treatment must be suspended (until the toxicity resolves to at least Grade 1) and the dose of abemaciclib must be reduced by 1 dose level as outlined in Table JPCE.7.2.

#### **7.4.1.1.1.4. Hepatic Toxicity**

Dose modifications and management for increased ALT/AST are provided in Table JPCE.7.2. For persistent or recurrent Grade 2 ALT/AST increase that does not resolve with maximal supportive measures within 7 days to baseline or Grade 1, or Grade 3 ALT/AST increase, abemaciclib must be suspended until the toxicity has resolved to baseline or Grade 1 and the dose must be reduced by 1 dose level. Discontinue abemaciclib for  $\geq$ Grade 2 increased ALT/AST ( $>3.0 \times \text{ULN}$ ) with total bilirubin (TBL)  $>2 \times \text{ULN}$ , in the absence of cholestasis. For Grade 4 ALT/AST increase, the patient must be discontinued from abemaciclib. Refer to Section 9.4.2.1 for additional hepatic monitoring guidance.

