| ALT/AST Increased
Sections 7.4.1.1.1.1.4 and 9.4.2.1                                                                                       | Persistent or recurrent b Grade 2 (>3.0-5.0×ULN) c , or Grade 3 (>5.0-20.0×ULN) d                                         | Dose MUST be suspended until toxicity resolves to baseline or Grade 1.                                                                                          | Dose MUST be reduced by 1 dose level.                                                                                         |
|                                                                                                                                               | Grade 4 (>20.0×ULN)                                                                                                                                        | Abemaciclib therapy MUST be discontinued.                                                                                                                       | Abemaciclib therapy MUST be discontinued.                                                                                     |

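### Table JPCE.7.2 and Section 7.4.1.1.1.4 set different mandatory triggers for suspending and reducing abemaciclib after Grade 2 ALT/AST increases

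*Protocol*

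**What the plan says.** In Table JPCE.7.2 (Section 7.4.1.1), the trigger in the ALT/AST row is a persistent or recurrent "Grade 2 (>3.0-5.0×ULN) c , or Grade 3 (>5.0-20.0×ULN) d". The action is "Dose MUST be suspended until toxicity resolves to baseline or Grade 1", with a mandatory reduction by one level. Three parts of the row and its footnotes matter:

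- Footnote c, attached here to Grade 2 only, reads "Note: the patient who presents with no liver metastases at baseline".
- Footnote b says "Determination of persistent events will be at the discretion of the investigator" and then "Recurrent toxicity refers to the same event occurring within the next 8 weeks (as measured from the stop date of the preceding event").
- The row mentions neither a number of days for resolution nor supportive measures.

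Section 7.4.1.1.1.4 (Hepatic Toxicity) opens by pointing to the table: "Dose modifications and management for increased ALT/AST are provided in Table JPCE.7.2". It then words the Grade 2 trigger itself: "For persistent or recurrent Grade 2 ALT/AST increase that does not resolve with maximal supportive measures within 7 days to baseline or Grade 1". The consequence is the same as in the table: "abemaciclib must be suspended until the toxicity has resolved to baseline or Grade 1 and the dose must be reduced by 1 dose level". Liver metastases are not mentioned.

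Neither place says which prevails. The two agree on Grade 3, on Grade 4, and on raised ALT/AST with raised bilirubin.

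**The concern.** Both passages are mandatory and lead to the same action, but they admit different patients to it. They differ in population (footnote c against no limit) and in time condition (investigator judgment or an 8-week recurrence window against 7 days without resolution). A site following the table and a site following the section can treat the same laboratory course differently, and each can claim compliance.

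This matters to the analysis because safety is the primary objective, and Section 10.3.4.4 summarizes dose omissions, reductions, delays and dose intensity. Table JPCE.7.3 offers one step down, and Section 8.1 lists an event that would cause a second reduction as a reason to stop study treatment. A reduction ordered under one wording only can therefore change both the exposure summaries and, indirectly, discontinuations.

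**Working it through.** No arithmetic applies and the protocol states no figure to reproduce. The check sets the two triggers side by side and classifies patient types under each. Throughout, the event is taken as related to abemaciclib (the condition Section 7.4.1.1 sets for the table), and bilirubin is taken as not raised enough to invoke the separate discontinuation rule.

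| Patient and course | Table JPCE.7.2 | Section 7.4.1.1.1.4 |
|---|---|---|
| 1. No liver metastases; Grade 2 recurs within 8 weeks and resolves within 7 days | Suspend and reduce | Not triggered |
| 2. No liver metastases; Grade 2 judged persistent before day 7 | Suspend and reduce at once | Only if unresolved after 7 days |
| 3. No liver metastases; persistent Grade 2 unresolved after 7 days | Suspend and reduce | Suspend and reduce |
| 4. Liver metastases; persistent Grade 2 unresolved after 7 days | Grade 2 trigger does not apply, on the natural reading of footnote c | Suspend and reduce |
| 5. Grade 3, any patient | Suspend and reduce | Suspend and reduce |

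The passages part in rows 1, 2 and 4.

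**Row 1.** Recurrence is fixed by date in footnote b, so investigator judgment of persistence cannot remove the conflict. Such a course can be observed: Section 9.4.2.1 asks for repeat liver tests within 2 to 4 days once ALT or AST reaches 3 times the upper limit in a patient who started below 1.5 times.

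**Row 2.** An investigator who uses 7 days as the mark of persistence satisfies both wordings, so the conflict is avoidable here.

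**Row 4.** The table does not leave this patient unmanaged. The opening sentence of Section 7.4.1.1.1.2 requires related nonhematologic toxicity to return to baseline or Grade 1 before each cycle. Unlike the sentences after it, it does not set ALT/AST aside. Table JPCE.7.4 uses the same recovery standard. With a baseline below Grade 2, the next 21-day cycle cannot start under either wording until recovery. What differs is whether dosing stops within the cycle and whether the reduction is mandatory.

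**Can the 7-day condition be read into the ALT/AST row?** The same table writes that condition out in its general nonhematologic row, which excludes ALT/AST. Its absence from the ALT/AST row is therefore a real difference.

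**The case against.** The best defence is that Section 7.4.1.1.1.4 defers to the table in its first sentence, so the footnotes come with the reference and the section merely omits a qualifier. That could settle the population. It does not settle the time condition, because the section adds one that the table lacks, and row 1 still diverges.

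A second defence is that footnote c is a sentence fragment and does not say that patients with liver metastases are exempt. This stands in part. A population limit is the natural reading, but it is a reading. If footnote c sets no limit, row 4 disappears and row 1 remains.

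A third is that consequences are softened. The text after Table JPCE.7.3 allows further reduction to be discussed with the sponsor's physician for a patient who benefits. Section 7.4.1.1.1.1 allows re-escalation after consultation, and Section 7.4.1.1 gives a route for questions. This also stands: a reduction made under one wording does not lead irreversibly to stopping treatment.

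Two stronger readings are tempting. A reader might infer that a patient with liver metastases and lasting Grade 2 ALT/AST is simply exempt under the table; the recovery requirement before each cycle rules that out. A reader might also count every patient with liver metastases as affected. The protocol gives no prevalence of liver metastases and no rate of Grade 2 events, and a patient is affected only on developing a qualifying event.

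**Conclusion.** The inconsistency is real and is in the current text. Section 3.1.5 describes amendment (e) as updating the hepatic section and the table together, so they were meant to match. The firm conflict is the patient without liver metastases whose Grade 2 rise recurs within 8 weeks and clears within 7 days: mandatory suspension and reduction under one passage, neither under the other. This takes the section's 7-day clause to govern recurrent as well as persistent events, as its grammar indicates. The conflict over liver metastases is narrower and rests on reading footnote c as a population limit.

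The number of patients affected cannot be derived from the protocol. It is the number with a related, persistent or recurrent Grade 2 ALT/AST event of the kinds in rows 1, 2 or 4, which may be small. That reported reductions would in fact vary by site is a risk created by the wording, not something the documents show. The point merits correction because two mandatory rules disagree in a trial whose primary objective is safety.

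**What to change.** Reconcile the ALT/AST row of Table JPCE.7.2 and its footnotes b and c with Section 7.4.1.1.1.4, so that both state the same population and the same time condition for persistent and for recurrent Grade 2 events. Complete footnote c as a full sentence. Which rule is adopted is a clinical decision for the sponsor, and none is proposed here. The cost is a wording change in the next amendment, with no change to the assessment schedule or the sample size.

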**7.4.1.1.1.5. Interstitial Lung Disease/Pneumonitis**

Dose modifications and management of ILD/pneumonitis are provided in [Table JPCE.7.2](#). If a patient experiences Grade 2 ILD/pneumonitis, then dosing must be suspended until the toxicity resolves to either baseline or Grade 1, and the dose of abemaciclib must be reduced by 1 dose level. If Grade 2 ILD/pneumonitis does not resolve with maximal supportive measures within 7 days to baseline or Grade 1, then abemaciclib must be discontinued.

For recurrent Grade 2 or Grade 3 or 4 ILD/pneumonitis, a patient must be discontinued from abemaciclib treatment. Refer to Section [9.4.2.4](#) for additional ILD/pneumonitis monitoring guidance.

**7.4.1.1.1.6. Venous Thromboembolic Events**

Dose modifications and management for VTE for patients with breast cancer are provided in [Table JPCE.7.2](#). For Grade 3 or 4 VTE, suspend abemaciclib dose and treat as clinically indicated. Abemaciclib therapy may be resumed when participant is clinically stable. Dose modifications for patients with lung cancer who experience VTEs should be managed using the nonhematologic toxicity guidance. Refer to Section [9.4.2.3](#) for additional VTE monitoring guidance.

**7.4.1.1.2. Pembrolizumab**

Adverse events (AEs; both nonserious and serious) associated with pembrolizumab exposure may represent an immunologic etiology. These AEs may occur shortly after the first dose or several months after the last dose of treatment. Pembrolizumab must be withheld (dose reductions are not permitted) for drug-related toxicities and severe or life-threatening AEs ([Table JPCE.7.5](#)). See Section [7.7.1.2](#) for supportive care guidelines for pembrolizumab, including use of corticosteroids (Section [7.4.1.1.2.2](#)).

**7.4.1.1.2. Dose Delays and Omission****7.4.1.1.2.1. Abemaciclib****Table JPCE.7.4. General Dose Delays of Abemaciclib**

| General Dose Delays                                                                                                         | Time Permitted for Delay |
|-----------------------------------------------------------------------------------------------------------------------------|--------------------------|
| Delay of a cycle due to holidays, weekends, bad weather, or other unforeseen circumstances                                  | 7 days                   |
| Toxicity-time for recovery to baseline or at least Grade 1 for nonhematologic and at least Grade 2 for hematologic toxicity | Up to 14 days            |

In exceptional cases, a dose delay >14 days is permitted upon agreement between the investigator and the Lilly clinical research physician.

## 7.4.1.1.2.2. Pembrolizumab

Table JPCE.7.5. Dose Modification Guidelines for Pembrolizumab

| Toxicity                                                 | Hold Treatment For Grade | Timing for Restarting Treatment                                                                                                    | Treatment Discontinuation                                                                                                                                         |
|----------------------------------------------------------|--------------------------|------------------------------------------------------------------------------------------------------------------------------------|-------------------------------------------------------------------------------------------------------------------------------------------------------------------|
| Diarrhea/Colitis                                         | 2-3                      | Toxicity resolves to Grade 0-1                                                                                                     | Toxicity does not resolve within 12 weeks of last dose or inability to reduce corticosteroid to 10 mg or less of prednisone or equivalent per day within 12 weeks |
|                                                          | 4                        | Permanently discontinue                                                                                                            | Permanently discontinue                                                                                                                                           |
| AST, ALT, or Increased Bilirubin (see Section 9.4.2)     | 2                        | Toxicity resolves to Grade 0-1                                                                                                     | Toxicity does not resolve within 12 weeks of last dose                                                                                                            |
|                                                          | 3-4                      | Permanently discontinue (see exception below) a                                                                         | Permanently discontinue                                                                                                                                           |
| Type 1 diabetes mellitus (if new onset) or Hyperglycemia | T1DM or 3-4              | Hold pembrolizumab for new onset Type 1 diabetes mellitus or Grade 3-4 hyperglycemia associated with evidence of beta cell failure | Resume pembrolizumab when patients are clinically and metabolically stable                                                                                        |
| Hypophysitis                                             | 2-4                      | Toxicity resolves to Grade 0-1. Therapy with pembrolizumab can be continued while endocrine replacement therapy is instituted      | Toxicity does not resolve within 12 weeks of last dose or inability to reduce corticosteroid to 10 mg or less of prednisone or equivalent per day within 12 weeks |
| Hyperthyroidism                                          | 3                        | Toxicity resolves to Grade 0-1                                                                                                     | Toxicity does not resolve within 12 weeks of last dose or inability to reduce corticosteroid to 10 mg or less of prednisone or equivalent per day within 12 weeks |
|                                                          | 4                        | Permanently discontinue                                                                                                            | Permanently discontinue                                                                                                                                           |
| Hypothyroidism                                           | 2-4                      | Therapy with pembrolizumab can be continued while thyroid replacement therapy is instituted                                        | Therapy with pembrolizumab can be continued while thyroid replacement therapy is instituted                                                                       |
| Infusion Reaction                                        | 2 b           | Toxicity resolves to Grade 0-1                                                                                                     | Permanently discontinue if toxicity develops despite adequate premedication                                                                                       |
|                                                          | 3-4                      | Permanently discontinue                                                                                                            | Permanently discontinue                                                                                                                                           |
| Pneumonitis                                              | 2                        | Toxicity resolves to Grade 0-1                                                                                                     | Toxicity does not resolve within 12 weeks of last dose or inability to reduce corticosteroid to 10 mg or less of prednisone or equivalent per day within 12 weeks |
|                                                          | 3-4 or recurrent 2       | Permanently discontinue                                                                                                            | Permanently discontinue                                                                                                                                           |
| Renal Failure or Nephritis                               | 2                        | Toxicity resolves to Grade 0-1                                                                                                     | Toxicity does not resolve within 12 weeks of last dose or inability to reduce corticosteroid to 10 mg or less of prednisone or equivalent per day within 12 weeks |
|                                                          | 3-4                      | Permanently discontinue                                                                                                            | Permanently discontinue                                                                                                                                           |

